#### Multiple testing

We will use alpha = .05 for each primary hypothesis. For multiple testing conducted within each main hypothesis, we will adopt a stepwise multiple comparison procedure that is considered more powerful than the widely used Bonferroni correction [93, 94].

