#### Missing data

Longitudinal analyses will use all available data and produce valid inferences if attrition depends on treatment group or on previous outcomes for the same participant [95]. If dropout is associated with other variables, they will be added as predictors to reduce bias due to data missing not at random.

#### Hypothesis 1

*CT + Memory Support will be superior to CT-as-usual for improving course of illness and reducing functional impairment at post-treatment, 6FU and 12FU on primary outcomes* listed in Additional file 1. Treatment groups will be compared on categorical outcomes (e.g., remission, relapse) using logistic regression to evaluate the odds of remission at post-treatment, and the odds of relapse at 6FU and 12FU. For the continuous variables (e.g., IDS-SR), we will test for differences in the mean trajectories across time between CT + Memory Support and CT-as-usual using Hierarchical Linear Modeling (HLM) [96–98]. The 1st level will represent within-person variation, and will include time indicators (or dummy variables) as predictors (post-treatment, 6FU and 12FU, with baseline as reference). The 2nd level represents between-person variation in the intercept and coefficients of the time indicators, and will include a dummy variable for arm (CT + Memory Support vs. CT-as-usual) as the predictor variable. Interactions between arm and the time indicators will be retained only if found to be significant at the 5% level using likelihood-ratio tests. Significant interaction terms between arm and time indicator suggest that there are different trajectories across time and between arms, and will be graphed to interpret the interaction.

#### Hypothesis 2

*Relative to CT-as-usual, the relationship between CT + Memory Support and better treatment outcome will be mediated by patient memory for treatment*. Outcome will be measured by IDS-SR at post-treatment, 6FU and 12FU. Patient memory will be measured by the Patient Treatment Recall Task and the Generalization Task at weeks 4, 8, 12 and 16 of treatment. A mediation model will be specified using Structural Equation Modeling [99]. Indirect effects from CT + Memory Support to better treatment outcome via patient memory will be assessed.

#### Hypothesis 3

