#### Power analysis

Based on the pilot study [34], using Glimmpse [104, 105] for repeated measures design, we took into account the four repeated measurements (pre-treatment, post-treatment, 6FU, 12FU). At an alpha level of 0.05 with 80% power, the sample size is estimated to be 80 for the IDS-SR. We also used G*Power and the Demidenko [106] method to calculate estimated sample size for binary mood outcomes (i.e., remission, relapse). The sample sizes are estimated to be 103 (remission) and 118 (relapse). Finally, Fritz and MacKinnon [107] provide recommendations for mediation sample size, and estimates from pilot data indicate that the recommended sample size is 148. Adding an additional 20% for possible attrition, we propose a sample of 178.

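### For the continuous outcomes, the arm-by-time terms that carry the Hypothesis 1 effects are kept only if significant; when they are dropped, the arm term left is averaged over baseline and estimates none of those effects.

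*Protocol article*

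**What the plan says.** All of this is in the protocol article, Data analysis.

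- Hypothesis 1 claims: "CT + Memory Support will be superior to CT-as-usual for improving course of illness and reducing functional impairment at post-treatment, 6FU and 12FU".
- For continuous outcomes, level 1 of the hierarchical linear model has "time indicators (or dummy variables) as predictors (post-treatment, 6FU and 12FU, with baseline as reference". Baseline is thus one of four modelled outcome occasions.
- Level 2 "will include a dummy variable for arm (CT + Memory Support vs. CT-as-usual) as the predictor variable". On the random part: "The 2nd level represents between-person variation in the intercept and coefficients of the time indicators".
- The selection rule is: "Interactions between arm and the time indicators will be retained only if found to be significant at the 5% level using likelihood-ratio tests". The only reading rule that follows concerns significant interactions, which are to be graphed. Nothing says which quantity answers Hypothesis 1 if they are not significant.
- Multiple testing: "We will use alpha = .05 for each primary hypothesis", and within each main hypothesis "we will adopt a stepwise multiple comparison procedure that is considered more powerful than the widely used Bonferroni correction". It is not said whether this covers the sequence of selecting terms and then testing.
- Power analysis: "At an alpha level of 0.05 with 80% power, the sample size is estimated to be 80 for the IDS-SR". The effect size, SD and correlation behind it are not given.

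**The concern.** With baseline as the reference occasion, the arm coefficient in the full model is the baseline difference between arms, which randomisation makes zero in expectation. The effects named in Hypothesis 1 are exactly the arm-by-time coefficients. The plan therefore uses a significance test to decide whether the terms holding the treatment effect stay in the model.

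Both branches do harm. If the terms go, the remaining arm coefficient mixes the null baseline difference with the three later differences, so it is pulled toward zero and matches no effect in the hypothesis. If the terms stay because they passed a test, the reported estimates have been selected for being large. For a trial that its Discussion presents as confirmatory, the main continuous analysis should yield the same estimand whatever the data show.

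The rule also sits awkwardly with the Preliminary data evaluation section, which declines to let statistical tests choose covariates in the primary analysis.

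**Working it through.** **The plan's own figures.** 148 × 1.2 = 177.6, rounded to 178, as stated. The IDS-SR figure of 80 cannot be rebuilt, because its inputs are not given. With 20% attrition, 178 × 0.8 = 142, or 71 per arm.

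**Assumptions, not in the article.** Follow-up SD 1; common correlation ρ; one joint likelihood-ratio test of the three arm-by-time terms (3 df, critical value 7.815).

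**1. What the leftover arm coefficient estimates.** With the interactions removed, it is a weighted mean of the four arm differences, with weights proportional to Σ⁻¹1.

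- Equal variances and correlations: each weight is 1/4. For a constant post-baseline effect δ the coefficient is (0 + 3δ)/4 = 0.75δ, so 0.40 SD becomes 0.30 SD.
- Baseline SD 0.7 (plausible given the entry cut-off of 26 on the IDS-SR). Let u = (1/0.7, 1, 1, 1), with sum 4.4286. Each weight is proportional to u × [u − 4.4286 ρ/(1 + 3ρ)].
  - ρ = 0.5: 4.4286 × 0.2 = 0.8857. Terms 0.7755 and 3 × 0.1143. Baseline weight 0.7755/1.1184 = 0.69, leaving 31% of the effect.
  - ρ = 0.3: 4.4286 × 0.1579 = 0.6993. Terms 1.0419 and 3 × 0.3008. Baseline weight 1.0419/1.9442 = 0.54, leaving 46%.
- Effects of 0.4, 0.2 and 0.1 SD with equal variances: (0 + 0.4 + 0.2 + 0.1)/4 = 0.175 SD, against 0.40 SD at post-treatment.

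**2. How often the terms are dropped.** Under equal variances the noncentrality for a constant effect is λ = (n/2) × 0.75δ²/(1 − ρ), with n per arm. For n = 71 and δ = 0.30: 35.5 × 0.0675 = 2.396, divided by (1 − ρ).

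| ρ | λ | Dropped |
|---|---|---|
| 0.3 | 3.42 | 69% |
| 0.5 | 4.79 | 58% |
| 0.7 | 7.99 | 35% |

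Now suppose instead that N = 80 is a total and refers to 80% power for this 3-df test. Then λ = 10.90 at N = 80 and 10.90 × 142/80 = 19.35 at N = 142, and the terms are dropped in about 3% of trials. The implied constant effect is √[10.90(1 − ρ)/(20 × 0.75)] = 0.71, 0.60 or 0.47 SD for ρ = 0.3, 0.5 or 0.7.

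**3. Type I error.** Under the null the interaction test and the arm test in the reduced model are asymptotically independent.

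- If both count as evidence at 5%: 1 − 0.95² = 9.75%. Simulation gave 10.0–11.1% at 74–89 per arm.
- If only the interaction test counts: nominally 5%, simulated 5.3–6.0% at 74–89 per arm.

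**4. The random part.** A random intercept and three random time coefficients have 10 variances and covariances; a free residual makes 11 parameters. A 4 × 4 covariance matrix has 10 distinct elements. The Jacobian has rank 10, so the marginal covariance is identified and only the split between random effects and residual is not.

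**The case against.** Four points can be made for the plan.

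**The doubled type I error is not stated.** A reader might infer that the plan runs two 5% tests. The article names a test of mean trajectories and gives a reading only for significant interactions. It never says that the arm coefficient is then tested for Hypothesis 1, and any such second test might be held to fall under the stepwise procedure. This stands: 9.75% is conditional. On the other reading, however, a non-significant result leaves no valid effect estimate.

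**The drop rate may be small.** A reader might infer that the terms would be lost in about half of trials. That rests on an assumed 0.30 SD effect found nowhere in the article; on the planning effect as read above, it is about 3%. This stands, so only a range can be given.

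**The rule does not always lose power.** At N = 142 and ρ = 0.5 with a constant 0.30 SD effect, either step is significant in 65% of trials, against 79% for a baseline-adjusted average contrast. With a fading 0.4, 0.2, 0.1 SD effect the order reverses, 66% against 58%, although the two-step figure carries the roughly 10% error rate. Part of the gap also reflects 3 df against 1 df and the baseline adjustment. A general claim of lost power is not supported.

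**The random part does not break the analysis.** A reader might infer that the model cannot be fitted and must be changed after the data are seen. The article does not say that the covariance is unstructured with a free residual. Even if it is, the marginal model and the fixed-effect tests equal those of an unstructured covariance.

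None of these answers the central point. The retention rule is explicit, applies to the terms that carry the effect, and is not repaired elsewhere in the article.

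**Conclusion.** Wrong as written, for the continuous outcomes only; the logistic analyses of remission and relapse are untouched. The stated coding alone establishes that the rule can remove the very coefficients Hypothesis 1 is about, and that what remains is averaged over baseline. This needs no assumed numbers.

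The sizes do need them. The leftover coefficient is 75% of a constant effect under equal variances and correlations, and 31–46% with a baseline SD of 0.7. Dropping ranges from about 3% to 69% of trials across the effects and correlations considered. The upward selection of retained estimates follows in direction but has not been quantified. Type I error is about 9.75% if the leftover arm coefficient is also tested for Hypothesis 1 without multiplicity control, and near 5% if it is not.

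**What to change.** In Data analysis, Hypothesis 1:

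1. Delete the retention rule and state that all arm-by-time terms stay in the model regardless of significance.
2. State that the arm contrasts in change from baseline at post-treatment, 6FU and 12FU are the tests and the reported estimates for Hypothesis 1, with the stepwise procedure in Multiple testing applied to them.

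Optional tidy-up: specify an unstructured within-person covariance in place of random coefficients on all three time indicators plus a residual. It gives the same marginal model without the redundant parameter.

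The cost is about two sentences of text. No extra data or participants are needed.

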## Background

Patients accurately recall only about one third of the recommendations made during a physician visit [1–8] and during a cognitive behavior therapy (CBT) session [9, 10]. In one study, 25% of patients remembered recommendations that were *not* made [1]. Recall is particularly poor for advice for health-behavior change [11]. Perhaps not surprisingly, poor memory for the content of treatment is associated with poor adherence to medical treatments for chronic conditions [12–16], which is known to be associated with worse outcome [17]. Also, poor memory for CBT is associated with poorer outcome [10].

We have offered various explanations for these findings [18]. First, even when memory is functioning optimally, fallibility is possible at initial encoding, storage or retrieval [19]. Second, a CBT treatment session is typically 50 min long, covers complex information, and can elicit negative emotion. Negative emotion is associated with attentional biasing and narrowing, which impacts encoding [20]. Third, the odds are stacked *against* people learning, generalizing and transferring knowledge to new situations; this is known as the transfer of learning problem [21, 22]. Fourth, memory deficits and biases are common across mental disorders [23–27] and memory deficits are associated with poorer memory for treatment [28, 29].

The good news is that the impact of memory impairment can be minimized. Memory encoding and retention can be markedly improved by the use of memory support techniques. This has been demonstrated in medical visits [13, 30], and among older adults [31] as well as for people with memory impairments associated with Alzheimer’s disease, vascular dementia [32] and frontal lobe dysfunction [33].

We developed and tested the Memory Support Intervention, which is designed to improve patient memory *for treatment*. This approach is *not* intended to have a direct effect on improving memory functioning per se. The Memory Support Intervention was distilled from the cognitive science and education literature based on carefully honed criteria [18]. A small underpowered trial has provided preliminary evidence that the intervention exerts a measurable effect on patient memory for treatment and demonstrates a clinical effect [34].

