The Memory Support Intervention has been developed to be “transdiagnostic” (relevant to a broad range of mental disorders) and “pantreatment” (relevant to a broad range of types of treatment). However, investigating these possible broader applications seems premature without first establishing efficacy, which is the aim of the study described in this paper. To create a platform for the “next step” in investigating the approach, we will recruit patients who meet diagnostic criteria for major depressive disorder (MDD) and focus on one biopsychosocial intervention—cognitive therapy (CT). If the results are promising, future directions will test the applicability to other kinds of interventions and disorders and in other settings.

Why focus on MDD? First, MDD is prevalent and causes impairment [35, 36]; second, there is a need to improve treatments for MDD because a proportion of patients do not recover and of those who do recover, the majority relapse [37]; third, memory is poor in MDD and is modifiable [38, 39]; fourth, preliminary data suggest that improving memory for treatment in MDD improves outcome [34, 40, 41].

Why focus on CT for MDD? CT for MDD is well articulated and has been widely studied. Meta-analyses confirm CT as a frontline treatment [42, 43]. Despite these impressive outcomes, there is room for improvement [44, 45].

This study protocol addresses two additional considerations. First, older age, lower intelligence and chronic depression each predict poorer response to treatment for depression, including CT [46]. Impairment in declarative memory is also associated with poorer outcome [47–50]. Moreover, fewer years of education has been associated with a positive response to CT + Memory Support relative to more years of education [34]. We hypothesize that all of these poorer response groups may derive special benefit from the Memory Support Intervention. Hence, while we expect all patients to benefit from the Memory Support Intervention, we have planned analyses to determine if these subgroups stand to gain the greatest advantage from experimental facilitation of memory for treatment. Second, there is evidence that improved mood in MDD is associated with improved declarative memory [51], although remitted MDD patients still exhibit significant memory deficits [23]. We have planned analyses to address this potential confound.

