## Method/design

### Study design and setting

This is a prospective randomized controlled study. Adults (*n* = 178) who meet criteria for MDD will be randomly assigned, in a 1:1 parallel group design, to CT + Memory Support or CT-as-usual (see Fig. 1 for a flow chart of the study design). Randomization is stratified by age (≤49, 50 + years) and depression chronicity (< 2 years, ≥ 2 years) [46]. Participants receive a battery of outcome measures pre-treatment and post-treatment (i.e., within 2 weeks after the final treatment session) and at 6 and 12 months’ follow-up. Additional assessments of patient and therapist memory for treatment take place in weeks 4, 8, 12 and 16 of treatment for the mediation analysis.

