### Data analysis

#### Preliminary data evaluation

Missing or aberrant data will be verified. Data will be audited for quality and completeness. Evaluation of distributions detects outliers and ensures that assumptions of planned analyses are met. Baseline differences between groups will be examined (e.g., IQ, demographics, psychiatric and medical comorbidity, medications). Statistical tests will not be used to select covariates in the primary intent-to-treat analysis [90–92]. Instead, the potential influences of baseline differences will be evaluated as moderators. If remedial training is given to a therapist whose adherence to the treatment protocol is not satisfactory, this will be included as a dummy-coded covariate in all analyses.

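### The Hypothesis 2 mediation model names no baseline memory covariate, although the protocol links poor memory to both poorer recall of treatment and poorer outcome, so run as described it can overstate or falsely declare mediation

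*Protocol article*

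**What the plan says.** All places are in the protocol article.

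- **Data analysis, Hypothesis 2.** The mediator: "Patient memory will be measured by the Patient Treatment Recall Task and the Generalization Task at weeks 4, 8, 12 and 16 of treatment". The outcome: "Outcome will be measured by IDS-SR at post-treatment, 6FU and 12FU". The estimand: "Indirect effects from CT + Memory Support to better treatment outcome via patient memory will be assessed". The method is structural equation modelling. No baseline covariate is named.
- **Background.** One paragraph says that "memory deficits are associated with poorer memory for treatment". A later one says that "Impairment in declarative memory is also associated with poorer outcome". Older age, lower intelligence and chronic depression are given as predictors of poorer treatment response.
- **Measures, Memory.** Declarative memory is measured by the Face-Name task and working memory by the N-Back. Hypothesis 3 uses baseline declarative memory, and Additional planned analyses uses pre-post change in both, so a pre-treatment value of each is planned.
- **Preliminary data evaluation.** Statistical tests will not select covariates for the primary intent-to-treat analysis; instead, "the potential influences of baseline differences will be evaluated as moderators". The one covariate set for all analyses is a remedial-training dummy.
- **Hypothesis 3.** Age, IQ, chronicity, declarative memory and education enter as moderators.
- **Power analysis.** Mediation gives the largest sample size requirement, 148.

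**The concern.** An indirect effect is the product of two paths, arm to recall (a) and recall to IDS-SR (b). Arm is randomised, so path a is protected. Recall is not randomised, so path b is an observational association within arms. Any pre-treatment characteristic that lowers recall and also worsens outcome will make recall look effective when it is not. The article names such a characteristic, poor memory, and measures it.

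Nothing else in the article closes this path. The moderation tests of Hypothesis 3 contain no recall term. The check under Additional planned analyses, on whether recall improves merely because memory deficits resolve, regresses change in recall on change in mood and in memory. It lies outside the mediation model and does not adjust for differences in memory that existed before treatment.

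The bias runs in the favourable direction, towards finding the hypothesised mechanism. At stake is the claim of Aim 2, which the Discussion presents as part of a definitive test of patient memory as a treatment target. The efficacy comparison of Aim 1 does not depend on it.

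**Working it through.** **The plan's own figure.** 148 × 1.20 = 177.6, rounded up to 178, reproduces the planned sample, so mediation drives the trial size. The 148 itself cannot be re-derived, because no path sizes are given.

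**Inputs from the article.** N = 148 (also 178); 1:1 allocation; alpha 0.05, taken as two-sided.

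**Assumptions (not in the article).** Standardised arm-to-recall path a = 0.26, with range 0.14 to 0.39. The central value was chosen because equal paths of 0.26 give about 78% power at N = 148 by the joint-significance test. True recall effect b = 0; direct arm effect 0.10. One baseline variable U has standardised links r1 with recall and r2 with outcome. Outcome is scored so that higher is better; on the IDS-SR the sign of r2 reverses.

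**Bias formula.** With U omitted, the expected recall coefficient is

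b* = r1 × r2 / (1 − a²), where 1 − a² = 1 − 0.0676 = 0.9324.

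At 0.3/0.3: b* = 0.09 / 0.9324 = 0.097, and the spurious indirect effect is 0.26 × 0.097 = 0.025. The simulated mean is also 0.025.

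**Hand check of the false-mediation rate at 0.3/0.3, N = 148.**

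1. Path a: expected z = (0.26 / √0.9324) × √148 = 3.28, so it is significant in about 91% of trials.
2. Path b: the residual variance of outcome is 0.99 − 0.097² × 0.9324 = 0.981. The standard error is √(0.981 / (0.9324 × 145)) = 0.085, so z = 0.097 / 0.085 = 1.13 and it is significant in about 20.5% of trials.
3. Both: 0.906 × 0.205 = 18.6%. Simulation gives 18.2%.

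**Simulated rates of falsely declared mediation** (8,000 trials per row, joint-significance test, a = 0.26, N = 148):

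| r1/r2 | U omitted | U in both equations |
|---|---|---|
| 0/0 | 4.1% | 4.1% |
| 0/0.3 | 4.9% | 4.5% |
| 0.1/0.1 | 4.6% | 4.5% |
| 0.2/0.2 | 7.1% | 4.6% |
| 0.3/0.3 | 18.2% | 4.5% |
| 0.4/0.4 | 46.5% | 5.3% |
| 0.5/0.5 | 80.8% | 4.9% |

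**Sensitivity.**

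- At 0.3/0.3, varying a from 0.14 to 0.39 moves the unadjusted rate from 7.7% to 21.7%.
- A Sobel test at 0.3/0.3 gives 8.6% unadjusted and 1.5% adjusted.
- A larger sample does not help: at N = 178 the unadjusted rates are 8.0% (0.2/0.2), 22.3% (0.3/0.3) and 56.5% (0.4/0.4).
- Separate simulations with an arm effect of 0.5 SD on recall gave about 4% (0.1/−0.1), 6% (0.2/−0.2) and 15-17% (0.3/−0.3) unadjusted.

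**When recall does have an effect.** With within-arm recall variance 1, the expected unadjusted coefficient is b + r1 × r2. For b = −0.25 and links 0.3/−0.2 it is −0.25 − 0.06 = −0.31, which is 0.06 / 0.25 = 24% too large. For 0.4/−0.3 it is −0.25 − 0.12 = −0.37, which is 48% too large. Simulation gave −0.309 and −0.371.

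**The case against.** The strongest reply is that the article is silent and has not decided against adjustment. It says only that a mediation model will be specified. It gives no path diagram and no covariate list, and such a list commonly sits in a full protocol or analysis plan that is not shown here. That stands. A reader might infer from "the potential influences of baseline differences will be evaluated as moderators" that adjustment has been ruled out, but that sentence follows one about covariate selection in the primary intent-to-treat analysis and does not mention the mediation model. Using the same variables as moderators under Hypothesis 3 does not exclude them from Hypothesis 2 either.

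A reader might also infer that age, IQ and chronicity confound the recall path because the Background ties them to poorer response, or because "Randomization is stratified by age (≤49, 50 + years) and depression chronicity". The article does not support this. It links them to outcome and nowhere to recall, and a variable linked to outcome alone produces no inflation (4.9% against 4.5%). Education appears only as a predictor of differential benefit from memory support. For N-Back the article supports a role in forming declarative memories, but states no direct link to outcome.

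Finally, every correlation above is assumed. Nothing in the article favours 0.3 over 0.1, and at 0.1/0.1 the problem is negligible.

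What remains is that the model, as far as it is described, omits the one variable that the article's own text ties to both mediator and outcome. That is a specific and correctable weakness, not just a missing detail.

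**Conclusion.** The concern holds for baseline memory. If Hypothesis 2 is run with only the variables it names, the indirect effect is open to confounding by pre-existing memory, in the direction of the hypothesis. Across the simulations at N = 148 with no true recall effect, the false-mediation rate is about 4-5% at links of 0.1/0.1, 6-7% at 0.2/0.2 and 15-18% at 0.3/0.3, rising further with stronger links. After adjustment it is about 4-5%. These figures rest on the assumed correlations, on an arm-to-recall effect of about 0.26 standardised (or 0.5 SD), on a single confounder and on the joint-significance test; a smaller arm effect or a Sobel test lowers them.

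The article does not show that the analysis will in fact be unadjusted, that age, IQ or chronicity would produce false mediation, or that the bias must be large. The point should be settled before analysis, because Aim 2 sets the sample size and carries the mechanistic claim.

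**What to change.** In Hypothesis 2, state that baseline declarative memory (Face-Name task), with baseline N-Back as a related memory measure, enters both the recall equation and the IDS-SR equation as a pre-specified covariate. Name the indirect effect from this adjusted model as the primary mediation result, show the unadjusted one beside it, and add a sensitivity analysis for residual confounding between mediator and outcome. Age and chronicity, as stratification factors, and IQ and education may be added for precision; the text should not present them as demonstrated confounders.

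The cost is wording only, since the measures are already planned before treatment. The indirect effect will probably be smaller and its apparent power lower. With a true effect of −0.25 and links of 0.3/−0.2 and 0.4/−0.3, simulated joint power fell from 83% to 77% and from 86% to 80%. The unadjusted figures are higher because they include the confounding.
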